### General rules of the statistical analyses

A consort diagram will be reported. (Figure 3) All analyses will be performed on a full intention-to-treat basis. The data file will be finalized 90 days after inclusion of the last patient.

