### Secondary efficacy endpoints

All analyses will be performed uncorrected as well as corrected for age, BMI & NRS categories type and severity of illness. Time to event analysis will be analyzed similarly as the primary endpoint. Proportion of patients requiring support of vital organ functions and distribution of duration of support will be analyzed by non-parametric or parametric testing depending on the normality of the distribution in the subgroup of patients for which support was needed. Proportions will be compared using chi-square testing. Results of repeated measurements will be analyzed using an appropriate model for longitudinal data.

a. Time to discharge alive from the hospital, with patients still in the hospital at closing of the data file censored at that time point; patients transferred to another hospital censored on the day of transfer; and non-survivors censored beyond the longest hospital stay of survivors and censoring time of patients still in the hospital at closing of the data file (90 days after last patient inclusion) over both treatment groups.

b. Time to final (alive) weaning from mechanical respiratory support with patients still on mechanical respiratory support at closing of the data file being censored at that time point and ICU non-survivors censored beyond the longest duration of mechanical respiratory support of the survivors and censoring time of patients still on mechanical respiratory support at closing of the data file (90 days after last patient inclusion) over both treatment groups.

c. Kidney failure: Proportion of patients in need for renal replacement therapy (RRT) during ICU stay; distribution of duration of RRT (for those patients requiring RRT); proportion of patients with a post-randomization diagnosis of new kidney injury/failure (defined by modified Risk, Injury, Failure, Loss, and End-stage Kidney (RIFLE) classification criteria as a plasma creatinine doubling or more during ICU stay) in both treatment groups.

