d. Need for pharmacological or mechanical hemodynamic support during ICU stay, and duration of such need. In addition, time to final (alive) weaning from all pharmacological or mechanical hemodynamic support in ICU will be analyzed, with ICU non-survivors censored beyond the longest duration of pharmacological or mechanical hemodynamic support of the survivors and censoring time of patients still on such support at closing of the data file (90 days after last patient inclusion) over both treatment groups.

e. Need for a tracheostomy during ICU stay.

f. Occurrence of infections during ICU stay: Number of patients with new infections and types of infection as specified in the study protocol and the duration of any antibiotics therapy initiated after randomization for those patients requiring antibiotics.

g. Cholestasis and liver dysfunction: Proportion of patients during the time window of the intervention and during the whole ICU stay presenting with cholestasis, defined as total bilirubinemia above 3 mg/dl or an increase to 150% of baseline value of gamma-glutamyltransferase or alkaline phosphatase. An increase of alanine or aspartate transaminases higher than 3 times the upper limit of normal will be considered as a marker of liver cytolytic damage. Proportion of patients presenting with such liver cytolytic damage during the time window of the intervention and during the whole stay in ICU will be compared. More subtle changes in liver enzymes will be analyzed by comparing the distribution of the highest values and the time course of the daily measurements.

h. Inflammation: Effect of the intervention on inflammation will be analyzed by comparing the distribution of the highest value reached during ICU stay and changes from baseline to the highest value and by comparing time profiles of daily C-Reactive Protein values.

i. Distribution of 6 MWD at hospital discharge in both treatment groups will be compared, as well as the proportion of patients unable to perform the test due to clinical reasons.

j. Proportion of patients independent for all ADL functions in both groups will be compared at hospital discharge. Hospital non-survivors will be analyzed as fully dependent for all functions.

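### RRT and antibiotic durations are tested only among patients who received the treatment, with no rule for deaths on it, so these p-values do not compare the randomized groups

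*Protocol article*

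**What the plan says.** The opening paragraph of Secondary efficacy endpoints in the protocol article sets a general rule: the duration of vital organ support is tested "in the subgroup of patients for which support was needed".

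- **Item c** applies it to renal replacement therapy (RRT): "distribution of duration of RRT (for those patients requiring RRT"). The same item lists "Proportion of patients in need for renal replacement therapy (RRT) during ICU stay" as an outcome, along with new kidney injury.
- **Item f** compares "the duration of any antibiotics therapy initiated after randomization for those patients requiring antibiotics", next to the number of patients with new infections.
- **Item d** compares the duration of hemodynamic support, which falls under the same users-only rule, and adds an analysis of time to alive weaning.
- **Item b** (ventilation) is a time-to-alive-weaning analysis, with "ICU non-survivors censored beyond the longest duration of mechanical respiratory support of the survivors". The added analysis in item d uses the same device.
- **Item i**: "Distribution of 6 MWD at hospital discharge in both treatment groups will be compared", together with the proportion clinically unable to do the test.
- **Item j** (ADL): "Hospital non-survivors will be analyzed as fully dependent for all functions".

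Items c and f contain no counterpart to the rules for deaths in items b, d and j. General rules of the statistical analyses states: "All analyses will be performed on a full intention-to-treat basis". The end of that section declares every endpoint significant at p of 0.05 or lower, without adjustment for multiplicity.

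**The concern.** Starting antibiotics after randomization is by definition a post-randomization event. Need for RRT is itself a listed outcome, although for some patients it may predate randomization. If one strategy prevents mild cases, the users left in that arm are the more severe ones and their courses are longer, so a benefit can appear as harm. If death on treatment simply ends the course, the arm with more deaths can appear to have the shorter treatment.

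Randomization does not protect a comparison within users. The plan nevertheless treats the resulting p-value like any other, and a reader of the clinical report could take it as an effect of the feeding strategy.

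**Working it through.** **The plan's own figure.** The only design figure that can be checked is the sample size. For ICU mortality of 20% versus 23%, two-sided 0.05 and 70% power:

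n per arm = [1.960·√(2·0.215·0.785) + 0.524·√(0.20·0.80 + 0.23·0.77)]² / 0.03² = (1.139 + 0.304)² / 0.0009 ≈ 2315

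This agrees with the stated 2320. The point does not depend on it, but 2320 per arm fixes the scale of the simulations.

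**Inputs for RRT.** From the document: 2320 per arm and a 0.05 threshold. Assumed, because the document gives none of these:

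- 9% of patients need RRT: 0.09 × 2320 ≈ 209 users per arm
- log-normal course, median 7 days, log-SD 1
- 45% die on RRT, and death cuts the course to 20–80% of its length
- Mann-Whitney test among users, 2000 trials per scenario

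In every scenario the strategy does not lengthen any patient's course on RRT. It only prevents some courses or changes deaths.

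| Scenario (change in one arm only) | Median among users, days | Trials showing longer RRT in that arm |
|---|---|---|
| No difference | 5.1 vs 5.1 | about 2–3% |
| 10% of courses prevented, exactly the shortest | 5.1 vs 5.8 | about 36% |
| 20% prevented, exactly the shortest | 5.1 vs 6.7 | about 84–86% |
| 10% prevented, at random from the shorter half | – | about 12% |
| 20% prevented, at random from the shorter half | – | about 46% |
| Prevention unrelated to duration | no shift expected | no inflation (4–5%, both directions together) |
| Deaths 45% vs 35%, same need | 5.1 vs 5.5 | about 11% |
| Deaths 45% vs 40%, same need | – | about 6–7% |

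The shift in the median has a simple cause. If the shortest 10% are removed, the median of the remainder is about the 0.10 + 0.90 × 0.5 = 55th percentile of the full set. With 20% removed it is about the 0.20 + 0.80 × 0.5 = 60th.

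**A second set of assumptions.** Here 8% need RRT (0.08 × 2320 ≈ 186 per arm), with exponential courses of mean 10 days, or 4 days if death ends them, and 4000 trials. Rejections are two-sided.

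- Equal need and 40% deaths in both arms: 4.9%.
- Deaths 40% vs 50%: 12.1%. The arm with more deaths looks 0.45 day shorter in median.
- Deaths 40% vs 55%: 18.6%, 0.64 day shorter.
- One arm has an extra 1% or 2% of all patients with mild RRT courses (mean 3 days): 11.4% or 26.6%. That arm looks 0.45 or 0.77 day shorter although nobody benefits.

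Both models agree in direction. The bias vanishes when need and deaths are equal between arms, or when prevention is unrelated to duration and deaths are equal. No calculation was made for antibiotics. The argument is the same, but its size is not known.

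**The case against.** The strongest reply has four parts.

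1. **Companion outcomes are planned.** The proportion on RRT, new kidney injury, the number with new infections and mortality will all be reported, so a reader would see fewer users or more deaths beside the durations. This stands as mitigation, but it does not correct the duration p-value.
2. **The article is condensed.** It does not say how a course ended by death is scored. A reader might infer that death is formally counted as a short, favourable duration. That is the likely default, not a written rule. What the text does fix is the user-only population.
3. **The problem should not be extended to all organ support.** A reader might infer from the general users-only sentence that ventilation and hemodynamic support share the defect in full. They do not. Item b is an alive-weaning analysis, and item d adds one to its duration comparison.
4. **6MWD is different.** A reader might infer that the plan restricts it to patients who performed the test. Item i does not say so. It gives no value for deaths, unlike item j, but it does compare the proportion clinically unable, which offsets part of the problem. The Data collection section has the test done only as far as feasible, so some results will also be missing for logistic reasons.

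It is also fair that an all-randomized measure says little about duration alone: with 9% on RRT, 91% of patients have zero RRT days.

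**Conclusion.** The point holds for the duration of RRT (item c) and of antibiotics started after randomization (item f). Both are tested at 0.05 among users only, without a rule for deaths, in a plan that promises full intention-to-treat and handles death explicitly elsewhere. For hemodynamic support it holds only for the duration comparison in item d, which stands beside a sound analysis. For 6MWD it is an inference from silence.

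The size cannot be fixed from the documents. Under the 9% assumption, a false finding of longer RRT occurs in about 12% to 46% of trials if 10% to 20% of courses are prevented at random from the shorter half, and in about 36% to 86% if exactly the shortest are prevented. The second range is an extreme and should not be quoted alone. Deaths of 45% versus 35% give about 11%, and some plausible situations give no inflation at all.

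These are secondary endpoints. The primary endpoint handles death explicitly, and no primary conclusion depends on these tests. The change is worth making because the plan already contains the remedy.

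**What to change.** - **RRT and antibiotics.** Report durations among users descriptively, without p-values. Base inference on all randomized patients in one of two ways. The first is time to final alive cessation, with non-survivors censored beyond the longest survivor duration as in items b and d. The second is days alive without the treatment over a fixed period, with deaths at the worst value. In both, non-users count as zero treatment days, and the analysis must state how the many ties at zero are handled.
- **Hemodynamic support.** Keep the alive-weaning analysis as the inferential one and make the user-only duration descriptive.
- **6MWD.** State the analysis population. Rank hospital deaths and clinically unable patients lowest, in line with item j, and treat tests missed for logistic reasons as missing.

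**Cost.** Wording and analysis of collected data: days of RRT and other support, medications during the ICU stay, and vital status are already recorded. Because medications are recorded for the ICU stay, a fixed period for antibiotics must say how time after ICU discharge counts.

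**Downside.** The all-randomized measures combine need, duration and death, and for RRT they largely reflect incidence and mortality. The descriptive user-only figures should therefore stay alongside.

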### Data collected at study entry

At baseline, data on demographic and clinical characteristics of the patients are obtained. Disease specific risk scores are calculated and co-morbidities and known use of important medications prior to admission are noted: these comprise, among others, Acute Physiology and Chronic Health Evaluation II score (APACHE II), presence of cancer, diabetes mellitus, kidney failure (Chronic Kidney Disease score), liver failure (Child classification), COPD (Gold classification), and heart failure (New York Heart Association Functional Classification ≥ 2). Sepsis upon admission is labeled as such using modified Bone criteria [30,31].

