### Randomization

The study has a prospective, randomized, controlled, parallel-group design. Consecutive patients are randomly assigned to one of the two treatment study groups, labeled "Early PN" or "Late PN", using sequentially numbered, sealed and opaque envelopes. Upon addition of the study site Jessa Hospitals, these envelopes were replaced by an identical digital system allowing central computerized randomization. Patients are stratified per study site according to 17 primary diagnostic categories on admission. The stratified groups were labeled as follows:

I Medical-ICU admissions: (a) respiratory; (b) cardiovascular; (c) renal; (d) hematological/oncological; (e) GI/hepatic; (f) metabolic; (g) neurological (h) other;

II Surgical-ICU admissions according to referral discipline (a) cardiac surgery (elective or urgent surgery) (b) complicated thoracic surgery; (c) complicated vascular surgery (d) complicated abdominal and pelvic surgery (e) complicated neurosurgery (f) trauma and burns (g) transplantation (h) neurological disease (i) other.

Randomization - in a one to one allocation ratio - was performed using permuted blocks of 10, information that remained unknown to bed-side physicians and nurses, responsible for patient recruitment and therapy assignment.

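### New kidney injury/failure is defined by creatinine doubling alone, so a patient who starts renal replacement therapy before doubling is not counted as a case in that outcome

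*Protocol article*

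**What the plan says.** All references are to the protocol article. Secondary efficacy endpoints, item c, lists three kidney outcomes:

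- The first is "Proportion of patients in need for renal replacement therapy (RRT) during ICU stay".
- The second is "distribution of duration of RRT (for those patients requiring RRT").
- The third is "proportion of patients with a post-randomization diagnosis of new kidney injury/failure", which a modified RIFLE rule defines "as a plasma creatinine doubling or more during ICU stay".

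On who is analysed, General rules of the statistical analyses states: "All analyses will be performed on a full intention-to-treat basis". On who can be enrolled, the exclusions under Patient eligibility for inclusion and recruitment name neither kidney failure nor RRT. Data collected at study entry lists "kidney failure (Chronic Kidney Disease score") among the baseline items, and Randomization has a renal category among the medical strata: "a) respiratory; (b) cardiovascular; (c) renal". Data collection following recruitment records the need for RRT and the number of days on it. Blinding of treatment allocation states that treating physicians are not blinded.

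**The concern.** Doubling is the only criterion in the definition. Nothing in the article makes the start of RRT an event, or says how creatinine is read once RRT is running. RRT removes creatinine, so starting it both indicates kidney failure and makes it less likely that the stated criterion is ever met. A patient treated before doubling can therefore be a severe case by any ordinary reading and a non-case in this outcome.

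The error depends on a treatment decision made by clinicians who know the allocation. If RRT is started earlier or more often in one arm, that arm loses creatinine doublings for a reason unrelated to how many patients have kidney injury. The outcome is tested at 0.05 without correction for multiplicity, so a difference produced this way could be reported as an effect of the feeding strategy, or a real effect could be masked.

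**Working it through.** The article gives no rate, power or sample size for any kidney outcome, so there is no figure of its own to reproduce. The logic comes from the text. The size is an illustration on assumed rates.

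**1. Reading the definition.** Consider a patient not on RRT at entry.

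| Course after randomisation | Needs RRT (first outcome) | New injury/failure (third outcome) |
|---|---|---|
| Creatinine doubles, no RRT | no | yes |
| Creatinine doubles, then RRT | yes | yes |
| RRT starts, doubling never reached | yes | **no** |
| Neither | no | no |

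The third row is the problem. The two marginal proportions do not give the number of patients with either event, because their overlap (the second row) is not reported. Patients already on RRT at entry also count in the first outcome, so new RRT cannot be read from it.

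**2. Share of patients affected.** Assume that 6-10% of patients start RRT and that 25-40% of those start before doubling.

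- Low end: 0.06 × 0.25 = 1.5% of all patients.
- High end: 0.10 × 0.40 = 4.0% of all patients.

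**3. Share of injury events missed.** Let p be the doubling rate and q the rate of RRT before doubling, both among patients not on RRT at entry. The missed share is q/(p + q). Take the wider assumed ranges p = 5-10% and q = 1-5%.

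- Lowest: 0.01/0.11 = 9%.
- Middle (p = 5%, q = 3%): 0.03/0.08 = 38%.
- Highest: 0.05/0.10 = 50%.

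**4. Distortion between arms.** Assume that RRT use differs by 2 points and that the same 25-40% start before doubling.

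- 0.02 × 0.25 = 0.5 point; 0.02 × 0.40 = 0.8 point.

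With 2320 per arm (Sample size calculation) and an event rate of about 6%, the standard error of the difference is √(2 × 0.06 × 0.94/2320) = 0.70 point. The distortion is therefore about 0.7 to 1.1 standard errors.

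**5. Effect on the test.** Use a chi-square test, two-sided 0.05, 2320 per arm, with no true difference in injury.

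- 10.0% v 9.5% observed: standard error √(2 × 0.0975 × 0.9025/2320) = 0.87 point and shift 0.57 standard errors. The chance of p ≤ 0.05 is about 0.09.
- 5.0% v 4.2% observed: standard error √(2 × 0.046 × 0.954/2320) = 0.62 point and shift 1.30 standard errors. The chance is about 0.25.
- A larger assumed differential: true injury 10% in both arms, with RRT before doubling in 3% v 4%. The outcome reads 7% v 6%, and the chance is about 0.28.
- An extreme one: RRT before doubling in 3% v 5%. The outcome reads 7% v 5%, and the chance is about 0.82.

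The last case needs a 2-point difference in RRT before doubling. That is 2.5 to 4 times the 0.5-0.8 point in step 4, so it is an outer bound and not an expectation.

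**6. Denominator.** If a share f of randomised patients is already on RRT at entry and cannot be a new case, the observed rate is (1 - f) × p. For p = 5% and f = 1-5% it is 4.95% to 4.75%.

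**The case against.** The strongest reply is that item c already covers these patients. It reports the need for RRT beside the creatinine outcome, so a patient started on RRT before doubling is not lost to the report, and an arm difference in RRT would normally be visible there. This stands in part, and it limits the weight of the point. It is not a full repair, because that proportion mixes new with pre-existing RRT and the either-event count cannot be recovered.

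A second reply is that a creatinine criterion is a laboratory measure, whereas RRT is started by an unblinded clinician, so adding it imports a subjective decision. The trade-off is real and is a reason to keep the creatinine-only result. It does not rescue the present rule, because the same unblinded decision already acts on it by suppressing creatinine.

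Third, the criterion is openly labelled as modified, no other part of the article contradicts it, and every rate used above is assumed. All of that is correct.

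A reader might go further and infer that keeping patients already on RRT in the denominator biases the comparison. The article sets no at-risk denominator, so full intention-to-treat would keep them. But their status precedes randomisation and is balanced in expectation, and step 6 shows only a slight dilution. A reader might also infer that creatinine swings between RRT sessions would be counted as doubling. Nothing in the article supports this, and the outcome requires a new, post-randomisation diagnosis.

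**Conclusion.** The point holds as a limited one. As written, the third kidney outcome classes a patient who starts RRT and never reaches doubling as having no new kidney injury/failure, and the separate RRT proportion only partly compensates. The direction and size of any distortion are unknown, because they depend on how RRT timing differs by arm and the article gives no rates. On the assumed rates it is about 0.5-0.8 point for a 2-point arm difference in RRT, around one standard error at this sample size.

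It would be tempting to conclude that the endpoint is likely to point the wrong way or to give a false signal. The documents do not support that: the high false-signal probability arises only under a much larger assumed differential. The matter concerns one component of one of ten secondary items (a to j) and affects neither the primary endpoint nor the sample size.

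**What to change.** Define new kidney injury/failure as plasma creatinine doubling or first start of RRT after randomisation, whichever comes first, among patients not on RRT at randomisation. Keep the creatinine-only result and the overall RRT proportion as separately reported components, and show new RRT on its own line. This changes only how the outcome is counted and says nothing about when RRT should be given.

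The cost is about a sentence in item c plus some derivation. The need for RRT and the days on it are recorded. The article does not state that RRT status at entry or the start date is a recorded field, so both must be derived from the daily records, which should be possible but has to be confirmed. There are two small downsides: RRT start is an unblinded clinical decision, which the retained creatinine-only result lets a reader check, and the denominator becomes slightly smaller.

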#### Data collection following recruitment

All medications received by the patients during ICU stay are registered. Every day the amount of kilocalories, lipids, proteins, carbohydrates delivered by either PN or EN are calculated from the PDMS in an automated manner and entered into the case report form (CRF). For calculation of the energy requirements, 50% of the gastric residual volume, which is being discarded by the bedside nurses, is considered to be EN calories not absorbed by the patient. Interruptions of EN delivery and predefined digestive intolerance are registered daily. Mechanical complications such as displacement or obstruction of the enteral feeding tube or the central venous catheters; and clinical complications such as pneumothorax, hemothorax and subclavian or carotid artery puncture are recorded daily. Number of ICU days with a central line in situ is also noted. In addition we record the need for and the number of days of mechanical ventilatory support, of mechanical and pharmacological hemodynamic support, of renal replacement therapies and placement of tracheostomy.

Blood samples (a subset of which are immediately stored on ice for future endocrinological measurements) are taken upon ICU admission and daily at 06:00 h until discharge from ICU or death. All whole blood glucose levels are measured on arterial blood using a blood gas analyzer on each ICU and are registered for later calculation of glucose metrics.

Analyses on blood and urine for the primary clinical analyses include routine chemistry, hematology, and markers of inflammation. Further metabolic, endocrine and inflammatory measurements planned on stored samples in the context of mechanistic analyses fall beyond the scope of this paper. In addition, for later mechanistic studies, a random selection of patients are prospectively and repeatedly screened for the presence of sludge or cholecystitis on ultrasonography.

All new infections of the lungs, the blood stream, the urinary tract and wounds are recorded by an infectious disease specialist. Bacteraemia is further classified by responsible pathogen and as catheter related blood stream infection versus other bacteraemia [33,34].

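### The bilirubin limb of the cholestasis endpoint has no entry condition and the transaminase rule is ambiguous, so patients already above the cut-off can count as events

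*Protocol article*

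**What the plan says.** The protocol article, Secondary efficacy endpoints, item g, reports two liver proportions, each over the intervention window and over the whole ICU stay.

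- **Cholestasis:** "Proportion of patients during the time window of the intervention and during the whole ICU stay presenting with cholestasis", which is "defined as total bilirubinemia above 3 mg/dl or an increase to 150% of baseline value of gamma-glutamyltransferase or alkaline phosphatase".
- **Liver cytolytic damage:** "An increase of alanine or aspartate transaminases higher than 3 times the upper limit of normal".

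A cut-off-free comparison is added: "More subtle changes in liver enzymes will be analyzed by comparing the distribution of the highest values and the time course of the daily measurements".

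Two other items in the same list are limited to new events. Item c includes the "proportion of patients with a post-randomization diagnosis of new kidney injury/failure", and item f the "Number of patients with new infections".

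Blood samples "are taken upon ICU admission and daily at 06:00 h until discharge from ICU or death" (Data collection following recruitment), so an entry value should be available.

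**The concern.** The two limbs of the cholestasis definition work differently. The enzyme limb needs a rise from the patient's own baseline. The bilirubin limb needs only a value above 3 mg/dl, so a patient who arrives above it qualifies in either arm. Such patients can be enrolled. Liver disease is not among the exclusions, GI/hepatic and transplantation are randomisation categories, and the Child class is recorded at entry.

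The transaminase wording is unclear. It may mean a rise after entry that takes the patient past the cut-off, or any value past the cut-off.

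Prevalent cases carry no information on the effect of feeding. Counting them pulls the risk ratio toward 1 and raises the common event rate, so a real difference in new liver dysfunction is harder to see. The Background names liver dysfunction as a risk of overfeeding, and the Discussion would read a neutral trial as showing that PN can safely be withheld. A diluted liver contrast would make a neutral finding on this endpoint harder to interpret.

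**Working it through.** **Entry conditions side by side**

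| Criterion | Tied to entry value or limited to new events? |
|---|---|
| Bilirubin above 3 mg/dl (item g) | No |
| GGT or alkaline phosphatase to 150% of baseline (item g) | Yes, by definition |
| Transaminases above 3 times the upper limit (item g) | Unclear |
| Kidney injury, creatinine doubling (item c) | Yes |
| Infections (item f) | Yes |

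The adjusted analysis (General rules of the statistical analyses) corrects for type and severity of illness, age, BMI and NRS. It contains no baseline liver value.

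**Inputs from the article.** 2320 patients per arm, 1:1 allocation, chi-square test, significance at 0.05 (taken as two-sided), all randomised patients analysed.

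**The plan's own figure.** The article gives no rate, effect or power for the liver endpoints. Its sample size does reproduce from the mortality inputs: 20 v 23%, two-sided 0.05 and 70% power need 2315 per arm, against 2320 stated. At 2320 the power is 70.1%.

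**Dilution model.** Let q be the share above the cut-off at entry and p the incidence of new events among the rest. Both are assumptions.

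- All randomised: event rate q + (1 − q)p, with 2320 per arm.
- At risk only: event rate p, with 2320(1 − q) per arm.
- Power = Φ[(d − 1.96·SE₀)/SE₁], where d is the risk difference, SE₀ the pooled and SE₁ the unpooled standard error.

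**One case in full: q = 4%, incidence 6 v 8%**

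- All randomised: 0.04 + 0.96 × 0.06 = 9.76%, and 0.04 + 0.96 × 0.08 = 11.68%. The difference is 1.92 points, the risk ratio 11.68/9.76 = 1.20, and the power 56.1%.
- At risk only: 2320 × 0.96 ≈ 2227 per arm. The difference is 2 points, the risk ratio 1.33, and the power 74.4%.
- Loss: 18.3 points.

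**Range**

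| Assumed incidence | q | Power, all randomised | Power, at risk only | Loss (points) |
|---|---|---|---|---|
| 6 v 8% | 3% | 60.4% | 74.9% | 14.5 |
| 6 v 8% | 5% | 52.3% | 74.0% | 21.7 |
| 15 v 18% | 3% | 71.4% | 77.4% | 5.9 |
| 15 v 18% | 5% | 66.9% | 76.5% | 9.6 |
| 30 v 34% | 3% | 79.7% | 82.0% | 2.4 |
| 30 v 34% | 5% | 77.2% | 81.3% | 4.0 |

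At q = 1% the loss is 5.3 points at 6 v 8%, 2.0 at 15 v 18% and 0.8 at 30 v 34%. In every case the at-risk analysis has more power despite its smaller denominator.

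**The case against.** **Only part of the definition is affected.** A reader might infer that cholestasis as a whole is scored on absolute cut-offs. It is not: a stable high GGT or alkaline phosphatase at entry is not an event. Nor does the text settle that prevalent transaminase elevations count, because it speaks of an increase. Both points stand, and they limit the concern to bilirubin plus one unclear phrase.

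**The loss may be small.** Cholestasis can be met through any of three markers at any time in the ICU, so its incidence could be high, and the loss is then a few points. The upper end of the range needs a rare outcome with nearly as many prevalent as new cases. The model is also simplified: it scores every prevalent patient as uninformative, yet such a patient could still meet the enzyme limb because of treatment. This stands. No single figure should be quoted.

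**Other analyses cover part of the gap.** Peak values and daily courses use no cut-off, and the adjusted analysis includes diagnostic category. This helps only in part. The sentence on peaks and courses names liver enzymes, not clearly bilirubin. Peak values also carry any elevation present at entry, and a diagnostic category is a crude stand-in for a baseline value.

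**The contrast with item c is not clean.** Need for renal replacement therapy in that item, and items d and e, are not limited to new events either. This is fair. The case rests on the bilirubin definition itself, not on a uniform rule elsewhere.

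**A stronger charge would be bias.** A reader might infer that prevalent cases favour one arm or inflate false positives. Randomisation balances them in expectation, so the documents do not support that. Item g also states no expected direction, so it cannot be called an endpoint chosen to show harm from early PN.

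**Conclusion.** The concern holds in limited form. As written, the bilirubin limb counts patients above 3 mg/dl at entry as events, and the transaminase rule leaves open whether it does the same. The consequence is a diluted ratio and lost precision on one secondary item, without bias between arms or a raised type I error. With 3 to 5% prevalent, the loss runs from about 2 to 4 points of power at 30 v 34% incidence to about 15 to 22 points at 6 v 8%. Prevalence and incidence are both assumed, so the direction is firm and the size is not. This is a worthwhile clarification of low priority.

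**What to change.** In item g:

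1. Count the bilirubin limb only as a first value above 3 mg/dl after randomisation, in patients at or below 3 mg/dl on the admission sample.
2. Count transaminase damage only as a first crossing of 3 times the upper limit, in patients at or below it at entry. This also settles the ambiguous wording.
3. Define the composite's denominator. Either leave patients above 3 mg/dl at entry out of the main cholestasis proportion, or keep them at risk for the GGT/alkaline phosphatase limb only. The power figures above correspond to leaving them out.
4. Report prevalent cases by arm as a baseline characteristic.
5. Keep the all-randomised proportion as a supporting analysis.

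The at-risk set is fixed by entry values, so the randomised comparison is preserved. The cost is a few sentences and a slightly smaller denominator for this endpoint. The admission and daily samples are already scheduled, so no further blood sampling is needed.
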